#### Exercise control group (Baduanjin Qigong)

2.4.2

For the exercise control group, Baduanjin Qigong will be applied. This is in consideration that the acceptance, feasibility, and effectiveness of Baduanjin Qigong as a mind–body exercise with low to moderate intensity to improve older adults’ depressive symptoms has been extensively demonstrated (58, 59). The exercise routine of Baduanjin includes body postures and motion, concentrative breathing, and a meditative state of mind (60). Participants will practice a set of Baduanjin exercises repeatedly during one session. The Baduanjin Qigong exercise will be taught by a qualified Baduanjin instructor from the Hong Kong Wushu Union with the assistance of student helpers. The content for the Baduanjin Qigong exercise is presented in Table 2.

**Table 2 tab2:** Intervention content of Baduanjin.

Baduanjin 2 sessions/week	Warm-up	Baduanjin section		Cool-down
Intensity	50–70% HRmax (1–3 RPE)			50–70% HRmax (1–3 RPE)
Week 1–2	10-min: stretching and dynamic movement	14 min	Practice the following 8 movements under the guidance of the instructor: Preparation posture. (1) Prop up the sky with two improved tri-jiao; (2) Draw a bow on both sides like shooting a vulture; (3) Raise a single arm to regulate the spleen; (4) Look back to treat five strains and seven impairments; (5) Shake the head and wag to expel Heart (Xin)-fire; (6) Pull toes with both hands to reinforce the kidney; (7) Clench one’s fist and glare to increase strength; (8) Rise and fall on tiptoe seven times to treat all diseases; Ending posture.	10-min: Light walking, stretching, abdominal breathing, and relaxation
Week 3–4		14 min 50 s		
Week 5–6		15 min 40 s		
Week 7–8		16 min 30 s		
Week 9–10		17 min 20 s		
Week 11–12		18 min 10 s		
Week 13–14		19 min		
Week 15–16		19 min 50 s		

HRmax, maximum heart rate; RPE, rate of perceived exertion.

#### Non-exercise control group (recreation workshops)

2.4.3

To control the influence of confounders (e.g., social aspects of group activities), participants in the non-exercise control group will receive a series of group-based workshops related to daily recreation. The workshop sessions will be identical to the exercise groups (e.g., frequency and duration of intervention, sub-group mode) but no formal exercise treatment. It covers four topics throughout the 16 weeks: music appreciation, gourmet food appreciation, popular tourist attractions worldwide, and painting appreciation. Each workshop will include both instructor-delivered knowledge sessions and group interaction sessions. The workshop content is presented in Table 3.

**Table 3 tab3:** Intervention content of the recreation workshop.

Workshop 2 sessions/week	Topic	Time
Week 1–2	Music appreciation	34 min
Week 3–4	Music appreciation	34 min 50 s
Week 5–6	Food appreciation	35 min 40 s
Week 7–8	Food appreciation	36 min 30 s
Week 9–10	Tourist	37 min 20s
Week 11–12	Tourist	38 min 10 s
Week 13–14	Painting and handicraft	39 min
Week 15–16	Painting and handicraft	39 min 50 s

### Intervention strategies

2.5

#### Implementation strategies

2.5.1

Following safe, supportive, active, and enjoyable principles (61, 62), a series of strategies will be employed during the intervention: (1) Participants in each group will be divided into two subgroups (24 participants in each subgroup). The sub-groups within the same intervention condition will differ in the timeslot for attending the sessions but share the same instructor and intervention venues; (2) exercise sessions will be performed in different small teams of maximum 4 participants in one team with similar physical fitness and maximum heart rate; (3) participants in exercise sessions will wear Polar Verity Sense heart rate monitors connected to the Polar GoFit application, which will be monitored by student helpers and displayed on a tablet screen for providing real-time feedback to participants during exercise; (4) participants will be asked to record their RPE immediately after the completion of HIIT interval or Baduanjin movement; (5) HIIT sessions will be performed with continuous music and the music tempo will be set as 120 to 140 bpm for HIIT sections, and 60–80 bpm for warm-up and cool-down sections (63). For Baduanjin Qigong, traditional Chinese music will be used during the exercise; (6) any adverse events (e.g., suffering acute illness or exercise injury) that occurred during the intervention will be tackled, referred to the emergency plan, and documented.

#### Recruitment and retention strategies

2.5.2

As suggested by previous studies with depressive older adults (64), several practical strategies will be adopted for participant recruitment and retention, including (a) emphasizing study benefits and promoting positive attitudes and beliefs for participating in the project (e.g., expected health outcomes, free physical fitness test), (b) applying several behavioural change techniques that facilitate the retention of participation (e.g., positive persuasion, verbal encouragement, WhatsApp reminder one day before the intervention session, heart rate feedback), (c) providing financial incentives and awards for completing all measurements of outcomes (HK$100 coupon for each participant who completes the measurements at each wave (T1-T3) and a total HK$1500 lucky draw award to three participants who complete all measurements of all waves), (d) arranging exercise or workshop venues near participants’ residences.

### Outcome evaluation

2.6

Outcome evaluations will be performed three times at pre-intervention (T1), post-intervention (T2), and 3 months after intervention completion (T3). All the data collection will be implemented at the elderly centre, except for saliva collection, which will be conducted at the participant’s home.

#### Primary outcome variable

2.6.1

##### Depressive symptoms

2.6.1.1

The Chinese version of the 15-item Geriatric Depression Scale (GDS-C) will be used to measure depressive symptoms (47). The GDS is the most widely used scale for detecting depression symptoms in older adults (Cronbach’s *α* = 0.81–0.83). Participants will be asked 15 items, such as “Are you satisfied with your life in the past week?.” Answers are given on a yes/no scale. The total score ranges from 0 to 15, where 0–4 = normal, 5–8 = mild depressive symptoms, 9–11 = moderate depressive symptoms, and 12–15 = severe depressive symptoms (36).

#### Secondary outcome variables

2.6.2

##### Salivary cortisol

2.6.2.1

Previous studies have suggested that the cortisol awakening response (CAR) can be a potential biomarker of depressive symptoms in older adults (10, 13, 65). Protocols for evaluating CAR vary across the literature (66). The decision on the appropriate number of saliva samples involves a cost/accuracy trade-off: more post-awakening samples (0, 15, 30, 45, 60 min) improve the accuracy of CAR estimation but also entail higher costs and greater participant burden (67). Minimal protocol with two samples (usually 0 and 30 min) is an acceptable method for assessing CAR dynamics, as adopted by previous research (12, 67). This approach is less burdensome for older adults to maintain compliance and is sufficient for calculating the delta (Sample 2 – Sample 1). Therefore, this study will employ a two-sample protocol. Saliva samples (2–3 mL) will be collected at awakening and 30 min after awakening, respectively, to capture the dynamic increase. Delta *Δ* of cortisol between 30 min post-awakening vs. awakening levels computed as the cortisol awakening response.

All participants will be provided with a printed instruction that adheres to guideline (66) and asked to follow the assessment instructions. Saliva samples will not be taken if participants are ill or have a fever. Participants will be instructed to refrain from eating, drinking, and brushing their teeth for at least 30 min before collecting saliva. In addition, participants will be asked to report their stress levels using a 5-point scale before saliva sample collection to decrease assessment bias (68). The collection procedure will involve subjects putting a cotton swab in the mouth for at least 4 min until the swab is soaked with sufficient saliva. Then, the cotton swab with saliva is placed back into the containers. Following the collection of samples, participants will be instructed to record the exact time of collection on the label. They should store the salivary collection tubes in the freezer zone of their home refrigerator to keep the salivary cortisol stable until transported to the research lab within 24 h after collection. All the uncentrifuged saliva samples in the lab will be stored at −20 °C until analysis. Saliva will be assayed for cortisol (μg/dL) concentrations by a registered laboratory using a high-sensitivity ELISA kit (69). The inter-assay coefficients of variation (based on low- and high-control samples) are set at 5% for cortisol (70). If saliva samples do not meet the collection requirement, for example, participants only submit a sample at one collecting time point and do not meet the required saliva volume to detect cortisol concentration, then the participants will be asked to redo the test.

##### Physical fitness

2.6.2.2

Fitness will be assessed using the Senior Fitness Test manual (71). It is a widely used measurement for physical fitness in aging populations (53). There are seven testing items measuring all the five dimensions of fitness, including body mass index (BMI), 30 s chair stand for lower limbs’ muscle strength, 30 s arm curl for upper limb muscle strength, 2-min step test for aerobic endurance, chair sit-and-reach test for lower body flexibility, back scratch test for upper body flexibility, and 8 ft. up-and-go test for mobility and dynamic balance (71). The reliability and validity of the testing items have been previously described in the Manual (71). The current study will follow the testing procedures outlined in this manual.

##### Sleep quality

2.6.2.3

The Chinese version of the Pittsburgh Sleep Quality Index (PSQI) will be used to measure sleep quality (72). The PSQI is a widely validated scale appropriate for use with older adults (73). The scale includes 24 items, covering seven domains: subjective sleep quality, sleep latency, sleep duration, sleep efficiency, sleep disturbance, daytime dysfunction, and use of sleep medications. Each domain score ranges from 0 (no difficulty) to 3 (severe difficulty) (Cronbach’s *α* = 0.83–0.85). A total score will be calculated, with a higher score indicating poorer quality of sleep (scoring > 5 denotes the sleep disturbance).

##### Quality of life (QoL)

2.6.2.4

The extensively validated Hong Kong Chinese WHO Quality of Life Scale Brief Version (WHOQOL-BREF) will be used to assess older adults’ QoL (74). The scale includes 28 items, covering four dimensions: physical health, psychological health, social relationships, and environment. Answers are given on a 5-point Likert scale, ranging from 1 (very poor) to 5 (very good) (Cronbach’s *α* = 0.73–0.84). The scale yields a score for each dimension and a total score, with higher scores indicating a higher quality of life.

#### Other measures

2.6.3

Socio-demographic information will be collected at baseline as potential confounders, including gender, age, marital status, occupation, education level, type of housing, family size, and household income. In addition, common chronic diseases (diagnosed by a doctor) will be collected at baseline.

### Process evaluation of the intervention

2.7

A process evaluation will be conducted to assess program implementation and gather participants’ perspectives on the intervention and data collection. A comprehensive framework for designing and reporting process evaluation of cluster RCTs will be used (75). The evaluation will target intervention effects, implementation, and overall satisfaction with the program using a 10-item 5-point Likert Process Evaluation questionnaire. In addition, the Exercise Acceptability Scale (76) will be used to evaluate the feasibility and acceptability of the intervention.

### Procedure

2.8

Figure 2 demonstrates the procedure of intervention development, participant recruitment, data collection, intervention implementation, and evaluation. The proposed study will be completed over 24 months, as shown in Figure 2. In brief, (1) intervention contents and practical strategies will be developed and modified by a steering group and evaluated in a 16-week pilot study. Implementation materials and evaluation plan of the intervention will also be completed at this step; (2) all older adults from elderly centres will be invited into the study and screened for eligibility for participation; (3) all eligible participants will receive the outcome evaluations (both primary and secondary) within 1 month before the implementation of the intervention (T1). Meanwhile, the HIIT group will participate in preparation sessions during this period; (4) during the 16-week intervention, participants in three groups will receive a WhatsApp reminder one day before the intervention session. The process evaluation will be conducted for each session and the overall intervention during the intervention; (5) two more outcome evaluations will be performed within 1 month immediately after the intervention and 3 months follow-up (T2 and T3).

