### Study design

2.1

This study will be a single-blinded three-group cluster-RCT to examine the effects of HIIT intervention on depression symptoms, physical fitness, sleep quality, and quality of life immediately after a 16-week intervention and the residual effects 3 months following completion of the intervention. A cluster random sampling method will be adopted to recruit the participants. With elderly centres used as a cluster unit for randomization and intervention, nine elderly centres in Hong Kong will be randomly assigned to three groups. Thus, participants will be randomly recruited and assigned through elder centres to one of three groups: a HIIT group, an exercise control group (Baduanjin Qigong), and a non-exercise control group (recreation workshops). Randomisation will be conducted using the random function available in Excel by a researcher who will not be involved in the participant recruitment and data collection. The block size for randomization will be 3, and the clusters within each block will be sorted by block number and a random number. Evaluation will be conducted at pre-intervention (T1), post-intervention (T2), and 3 months after intervention completion (T3). Outcome assessors will be blinded to the intervention assignment results. The CONSORT flow diagram (46) is presented in Figure 1.

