Week 13–14		19 min 60 s HIIT work x 10 intervals + 60 s active recovery x 9 intervals	HIIT work (10 movements) (1) *slams*; (2) side-step and prison squat; (3) squat jumps; (4) *lunge and knee drive*; (5) Heisman; (6) lateral lunges and touch down; (7) *reverse lunge*; (8) *seal jacks*; (9) fast running; (10) low skater jumps. Active recovery: Step-on	
Week 15–16		19 min 50 s 65 s HIIT work x 10 intervals + 60 s active recovery x 9 intervals	HIIT work (10 movements) (1) *lunge kick*; (2) side-step and prison squat; (3) squat with calf raise; (4) lunge and knee drive; (5) *twist jump*; (6) *slam and straight leg touch*; (7) butt kicks; (8) seal jacks; (9) low skater jumps; (10) *curtsy lunge.* Active recovery: Step-on	

HIIT, high-intensity interval training; HRmax, maximum heart rate; RPE, rate of perceived exertion.

The movement in italics indicates the new movement, which differs from the previous session.

A preparation session will be conducted at the research lab one month prior to the formal HIIT program. All participants in the HIIT group (*n* = 48) will initially have their HRmax estimated using an age-related prediction equation (54). Then, participants will be thoroughly familiarized with the 38 movements of the HIIT exercise and the entire HIIT procedure. Finally, participants will be asked to implement the HIIT program (30s HIIT work x 10 intervals + 60s active recovery x 9 intervals), where they will need to adjust their individual movement speed to reach the required HIIT intensity.

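### HIIT-only preparation sessions share the month of the baseline (T1) assessments, and nothing requires T1 to come first

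*Protocol article*

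**What the plan says.** Protocol article, section 2.8 (Procedure), step 3, sets the baseline window: "all eligible participants will receive the outcome evaluations (both primary and secondary) within 1 month before the implementation of the intervention (T1". The next sentence reads "Meanwhile, the HIIT group will participate in preparation sessions during this period".

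Section 2.4.1 dates the preparation differently: "A preparation session will be conducted at the research lab one month prior to the formal HIIT program". It applies to the whole arm ("All participants in the HIIT group (*n* = 48) will initially have their HRmax estimated using an age-related prediction equation"). It includes familiarisation with 38 movements and ends with a complete bout: "participants will be asked to implement the HIIT program (30s HIIT work x 10 intervals + 60s active recovery x 9 intervals". Sections 2.4.2 and 2.4.3 describe no comparable session for Baduanjin or the workshops.

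On allocation, section 2.1 says "nine elderly centres in Hong Kong will be randomly assigned to three groups" and that "participants will be randomly recruited and assigned through elder centres to one of three groups". It blinds the outcome assessors and keeps the person who randomises out of recruitment and data collection. The steps in section 2.8 contain no randomisation or disclosure step.

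Section 2.9 fits a mixed model with time, group and their interaction, with baseline as one of the time levels. Baseline values are added as covariates only where they differ significantly between groups.

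**The concern.** A session given only to the HIIT arm tells its participants which arm they are in. If it falls before a participant's T1 visit, that baseline is no longer a pre-allocation, pre-exposure measurement. The primary outcome is the self-reported GDS, so blinding the assessor does not protect it from the participant's own knowledge. The fitness tests and cortisol could also follow a first high-intensity bout.

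T1 is the reference level of the time-by-group interaction. A shift in HIIT's T1 alone would look like a treatment effect, or would mask one, in HIIT versus Baduanjin and HIIT versus workshop. Both hypotheses in the Introduction include HIIT. Once collected, such a baseline cannot be restored in the analysis.

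**Working it through.** **Timing, side by side**

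- Section 2.8: T1 falls within the month before the start, and HIIT preparation falls in the same period.
- Section 2.4.1: preparation is placed a month ahead of the programme. Read literally, that is the opening of the T1 window; read loosely, it is anywhere in the window.
- Figure 2 caption: each outcome evaluation lasts one month, so the overlap is not confined to a day or two.
- No section puts T1 before preparation or before disclosure.

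Following the text as written therefore permits T1 after preparation for some or all HIIT participants.

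**Plan figures used**

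From section 2.3: 9 clusters × 16 = 144, or 48 per arm; ICC 0.01; attrition 30%. The design effect is 1 + (16 − 1) × 0.01 = 1.15. The total can be reproduced: the repeated-measures interaction calculation with f = 0.25, 90% power and zero correlation between measurements needs 87, and 87 × 1.15 / 0.70 = 142.9, in line with 144. The plan does not state that correlation; at 0.5 the same calculation gives 45, then 45 × 1.15 / 0.70 = 73.9. The timing point does not depend on this, but rho below has to be an assumption.

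**How a T1 shift passes through**

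Let s be the mean T1 shift in the HIIT arm, in SD units, and rho the correlation of baseline with the later score. If only a fraction of HIIT participants are measured after preparation or disclosure, s is that fraction times their individual shift.

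- Change from baseline (the time-by-group contrast): bias of size s.
- Baseline as covariate: bias of size rho × s.
- Baduanjin versus workshop: no bias from the preparation session.

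**Illustration with no true effect**

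Effective participants per arm: 48 × 0.70 / 1.15 = 29.2, so √(2/29.2) = 0.262.

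- Standard error, change scores: √(2(1 − rho)) × 0.262, which is 0.262 at rho = 0.5.
- Standard error, baseline as covariate: √(1 − rho²) × 0.262, which is 0.227 at rho = 0.5.
- Two-sided error = 1 − Φ(1.96 − b) + Φ(−1.96 − b), where b = bias / standard error.

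| Assumed shift s (rho = 0.5) | b, change | Error, change | b, covariate | Error, covariate |
|---|---|---|---|---|
| 0.1 SD | 0.38 | 6.7% | 0.22 | 5.6% |
| 0.2 SD | 0.76 | 11.9% | 0.44 | 7.3% |
| 0.3 SD | 1.15 | 20.9% | 0.66 | 10.2% |

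For s = 0.2 with change scores, the error is 9.9% at rho = 0.3 and 16.7% at rho = 0.7. At rho = 0, the value that reproduces 144, it is 8.4%.

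**Does the covariate rule in section 2.9 help?**

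At T1, before attrition, there are 48 / 1.15 = 41.7 effective participants per arm. The standard error of a pairwise baseline difference is √(2/41.7) = 0.219 SD. For s = 0.2, b = 0.2 / 0.219 = 0.91, which reaches significance about 15% of the time. The rule would usually not be triggered, and when it is, rho × s remains.

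**The case against.** The text shows overlap within a month, not a wrong order. A HIIT participant assessed before preparation, and before learning the allocation, is unaffected, and the team may intend exactly that. The GDS example item in section 2.6.1.1 asks about the past week, so a large shift from one session is not self-evident. Assessors are blinded, which gives some protection to the fitness tests. Figures 1 and 2 could not be read in the text reviewed and may show the sequence. All of this stands, and it means that contamination is possible rather than demonstrated. It does not remove the point, because the overlap is written into section 2.8 and no rule resolves it.

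A reader might go further in three ways that the documents do not support.

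- **Different people enrolling by arm.** The preparation sentence concerns people already enrolled. Section 2.8 lists invitation and screening before T1, the abstract speaks of eligible participants being allocated, and section 2.1 fixes no order. Differential enrolment does not follow.
- **Every effect estimate being biased.** Only contrasts involving HIIT are exposed to the session, and only through participants measured after preparation or disclosure.
- **A shift as large as a medium effect.** The documents give no figure for any shift, and its direction is open. If preparation lowered baseline GDS, the bias would run against HIIT.

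**Conclusion.** The point holds for the order of events at baseline. As written, sections 2.4.1 and 2.8 allow the HIIT arm, and only that arm, to give its baseline after learning its allocation and after a complete HIIT bout. Neither assessor blinding nor covariate adjustment conditional on significance reliably repairs this for a self-reported primary outcome.

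The error rates of about 7% to 21% are a sensitivity range. They rest on assumed mean shifts of 0.1 to 0.3 SD, rho = 0.5, the plan's own ICC and attrition, and a normal approximation. They show what could happen, not that a shift will occur. The sample size is not called into question by this point.

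**What to change.** State one sequence in sections 2.1, 2.4.1 and 2.8: consent and all T1 assessments at a centre, including home saliva collection, are completed before that centre's allocation is disclosed to its participants, and HIIT preparation takes place only after T1 is complete. Reconcile the preparation date in section 2.4.1 with the period given in section 2.8, and the single session in the former with the plural in the latter.

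The cost is tighter scheduling within the pre-intervention month and possibly a slightly longer gap between T1 and the start. Sample size and intervention content do not change. Holding back disclosure until several centres have all finished T1 is not needed, and under the two-month recruitment in the Figure 2 caption it could strain the one-month T1 window.
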